## Abstract

Given that golf tournaments last approximately five hours without an intermission, mental fatigue has become a critical factor affecting performance. Although research has shown that music intervention can effectively alleviate mental fatigue, this method has yet to be applied in golf. Therefore, this study aims to evaluate the effects of music intervention on golf-specific skill performance under mental fatigue. This study adopts a randomized, controlled, partially-blind design, including three groups. The MF-Mu group undergoes a mental fatigue induction task followed by a music intervention. The MF-nMu group completes the same mental fatigue task but does not receive the music intervention. The CON group serves as the control and receives neither the mental fatigue task nor the music intervention. Controlled variables include immersion tendency, sport anxiety, attention, motivation, and perceived exertion. Primary outcome measures include mental fatigue, driving shot, iron shot, chipping shot, and putting performance. Performance measures include accuracy and shot quality. In this study protocol, the use of smartphones for music intervention enhances its portability, allowing the intervention to be initiated or terminated at any time, increasing its flexibility and acceptability. Moreover, briefly listening to music during non-striking moments complies with golf regulations, making this study highly practical. It provides an effective strategy for golfers to manage mental fatigue in competitive environments.

Trial registration

ClinicalTrials.gov NCT06952283

## Introduction

One of the biggest differences between golf and other Olympic sports is the complex playing environment and long duration of competitions. Specifically, golf courses incorporate various natural elements (such as undulating terrain, bunkers, water hazards, and vegetation) [1–3], which contribute to its strategic complexity [4–7]. Additionally, each round of golf takes around five hours without a halftime break, during which golfers need to maintain attention and cognitive effort for extended periods [8–12]. Long periods of cognitive tasks, emotional challenges, and stress can lead to mental fatigue [13–15]. Symptoms of mental fatigue include mental exhaustion, lack of energy, feelings of tiredness, decreased attention, and impaired cognitive and behavioral performance [16–18]. In sports, mental fatigue can damage athletes’ physical, psychological, tactical decision-making, and sport-specific skill performance [19–21]. Research on mental fatigue in basketball and soccer is relatively well-developed [22,23], with various effective strategies proposed to recover from mental fatigue and enhance performance [24]. However, research in the field of golf, particularly regarding mental fatigue recovery strategies, is still scarce [25,26]. Therefore, conducting research on mental fatigue recovery and performance enhancement for golf athletes is of significant importance.

Many studies have shown that the negative impact of mental fatigue on skill performance may be attributed to a reduction in dopamine transmission, which adversely affects executive functions [21,27–29]. Dopamine plays a central role in reward, motivation, cognition, and motor control in the brain [30], and is one of the most commonly proposed mechanisms related to mental fatigue [31,32]. This theory suggests that prolonged mental exertion may lead to the accumulation of the neuromodulator adenosine, which increases the perception of effort in subsequent activities [31–33]. Martin et al. [20] further expanded this hypothesis, stating that adenosine accumulation inhibits dopamine release in the anterior cingulate cortex, thereby reducing motivation or the willingness to exert effort. Consequently, some researchers have suggested that recovery strategies targeting dopamine system modulation, such as music and caffeine, may be effective for combating mental fatigue [18,33]. However, nutritional supplements like caffeine [34,35], carbohydrate mouth rinses [36,37], and creatine [38], while helpful in alleviating mental fatigue, have delayed effects, carry economic costs with frequent use, and may affect sleep quality (such as caffeine) or increase body weight (such as creatine), making them unsuitable for long-term use [39]. In contrast, finding alternative methods that produce immediate effects and are cost-effective for reducing mental fatigue is crucial. Therefore, non-invasive brain stimulation may be an effective strategy to address mental fatigue [39].

Music therapy, as a non-invasive and low-risk intervention, has already achieved significant results in the medical field [40–44]. A large body of research has demonstrated that music therapy can effectively reduce anxiety, improve depressive symptoms, and help patients alleviate physical pain [42,43,45]. Additionally, a systematic review of 139 studies (involving 3,599 participants) by Terry et al. [46] found that listening to music significantly improved participants’ positive emotional experiences, reduced subjective fatigue, and enhanced physical performance. Music intervention strategies have been successfully applied to basketball players, with studies showing that music relaxation can help basketball players quickly recover from states of self-exhaustion and maintain performance [47] However, music intervention strategies have not yet been applied to golfers [24,48].

Therefore, the aim of this study is to investigate the impact of music intervention on the golf-specific skill performance of Chinese golfers under mental fatigue. Through experimental research, the study will analyze whether music intervention can effectively mitigate the negative effects of mental fatigue and enhance the performance of golfers’ specialized skills. Additionally, the study will examine the differential impact of mental fatigue and music intervention on various skills. The findings will not only provide practical strategies for golf coaches and athletes to recover from mental fatigue and improve competitive performance under such conditions, but also offer valuable insights for other sports that require high concentration and resilience under pressure.

## Methods and design

### Status and timeline

This study protocol has been approved by the Ethics Committee of Henan University, China (Approval No.: HUSOM2025−066) and strictly adheres to the ethical principles of the Declaration of Helsinki. Additionally, this trial was registered on ClinicalTrials.gov in April 2025 under the identifier NCT06952283. Fig 1 presents an overview of the study timeline. At present, neither participant recruitment nor data collection has commenced. The study is scheduled to begin participant recruitment on October 1, 2025, with recruitment expected to be completed by October 31, 2025. Data collection is anticipated to be completed by November 30, 2025, and the goal is to complete data analysis and obtain study results by December 31, 2025. Subsequently, we plan to disseminate the results to the broader public through publications in reputable peer-reviewed scientific journals and presentations at academic conferences

**Fig 1 pone.0337905.g001:**
[figure not shown]
SPIRIT schedule of enrollment, interventions, and assessments.

### Participants

Following recommendations from Lakens [49] and Aberson [50], powering for interaction effects is considered essential in behavioral intervention trials where the primary interest lies in differential changes across conditions. Accordingly, the sample size calculation is based on the statistical power required to detect a time × group interaction effect, estimated using the “ANOVA: Repeated measures, within–between interaction” model in G*Power 3.1. Assuming a medium effect size f = 0.25 (Cohen’s standard), α = 0.05, power = 0.95, three groups, two measurement time points, and an intra-class correlation (ICC) of 0.5, the estimated result shows that the study requires at least 66 participants (22 per group) to ensure sufficient power for detecting the interaction effect. Considering a potential dropout rate of 15% [51], a total of 76 golfers will be recruited. If practical resource constraints result in a slightly smaller sample size, the study will report effect sizes and Bayes factors to supplement the interpretation of statistical significance and cautiously delimit the generalizability of conclusions to ensure the scientific rigor and interpretability of the results.

Participants in this study will be selected from the National Colleges and Universities Golf Championship (NCUGC) in China. The research team will collaborate with the head coaches of the participating teams to determine the universities willing to participate. Subsequently, the head coaches and team physicians will conduct an initial screening of players based on the inclusion criteria set for this study (Table 1). The research team will then verify the eligibility of the selected participants before the experiment begins.

**Table 1 pone.0337905.t001:** Participant selection criteria.

Inclusion criteria	Exclusion criteria
Aged 18–24 years old	Color blindness
Golfers of the NCUGC	Hearing loss
Least 3 years of specialized golf training	Insomnia
Least 5 trainings per week	Experiencing any physical injury
	Experiencing mental health issues
	Receiving any medication

To ensure the safety of all participants, a team physician will be present throughout the experiment to provide immediate medical support and guidance in case of discomfort or injury. All participants are covered by accident and medical insurance provided by their universities. Before the experiment begins, the research team will provide participants with a detailed explanation of the study’s objectives, procedures, and potential risks, and obtain written informed consent.

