### Statistical analysis

All statistical tests will be conducted at a significance level of α = 0.05, with effect sizes measured using partial eta squared (η²p). The statistical power is set at 0.80, and all analyses will be performed using IBM SPSS Statistics 27.0. This study will adopt a 2 (Time: pre-test vs. post-test) × 3 (Group: mental fatigue–music intervention group, mental fatigue–non-music group, control group) mixed-design repeated measures ANOVA to examine the effects of mental fatigue and music intervention on golf-specific skill performance. The core hypothesis of the study is the time × group interaction effect, which aims to determine the performance differences across groups before and after the intervention, thereby verifying the potential value of music intervention under mental fatigue. Time main effects and group main effects will serve as secondary analysis objectives.

Prior to the main analysis, a one-way ANOVA will be conducted to compare baseline skill performance across the three groups to assess initial group equivalence and ensure the validity of subsequent comparisons. In the main effects analysis, mixed-design repeated measures ANOVA will be used to test the time main effect (whether overall skill performance changes over time), group main effect (whether there are overall differences among the three groups), and the time × group interaction effect (whether skill performance changes differ among the groups). If the assumption of sphericity is violated, the Greenhouse-Geisser or Huynh-Feldt correction will be applied to adjust the degrees of freedom. If the interaction effect is significant, simple effects analysis will be conducted to clarify the performance trends before and after the intervention within each group and to compare differences between groups at each time point.

To control the accumulation of Type I error due to multiple comparisons, all post hoc group comparisons will apply Bonferroni correction. If the study involves multiple primary outcomes or multiple independent hypothesis tests, the Holm-Bonferroni method will be further applied to control the family-wise error rate. In addition, the study will predefine a single primary outcome—ball-shooting accuracy score—while other technical indicators such as shot quality and reaction time will be treated as exploratory outcomes, serving to support and interpret the results but not as primary hypothesis testing targets.

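### The 95% power for a medium effect holds only on G*Power's default scale; on the partial eta squared scale to be reported, 66 golfers are powered for about 0.20, not 0.06

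*Protocol article*

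**What the plan says.** The Participants section bases the sample size on the time × group interaction, using the repeated-measures within–between interaction "model in G*Power 3.1". The inputs are "Assuming a medium effect size f = 0.25", justified only by reference to Cohen's standard, then "α = 0.05, power = 0.95, three groups, two measurement time points" and "an intra-class correlation (ICC) of 0.5". The stated result is at least 66 participants, 22 per group, raised to 76 for dropout. The article does not say which of G*Power's effect-size definitions was used, and it cites no golf data for the effect size.

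The Statistical analysis section makes the interaction the core hypothesis, runs all analyses in SPSS 27.0, and reports results "with effect sizes measured using partial eta squared (η²p"). It adds Cohen's d for between-group differences and Bayes factors. It nowhere converts f = 0.25 to the partial eta squared scale.

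**The concern.** The letter f stands for different quantities in a repeated-measures design. G*Power's default f for the interaction compares the spread of the cell means with the outcome SD, before the correlation and the number of time points enter. The f that corresponds to SPSS's partial eta squared already contains both. The same value, 0.25, is a much larger effect on the first scale than on the second.

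The sample size paragraph uses one scale and the results will be reported on the other, with no conversion between them. A reader who sees 95% power for a medium effect, and then a table of partial eta squared values, will naturally compare those values with 0.06. If the trial was sized for about 0.20, a non-significant interaction supports much less than that reader would think.

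**Working it through.** **Inputs.** From the Participants section: f = 0.25, α = 0.05, power 0.95, k = 3 groups, m = 2 time points, ρ = 0.5, N = 66, recruitment 76. From the Statistical analysis section: partial eta squared (η²p) from SPSS.

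**1. Reproduce 66.** On G*Power's default scale:
- λ = f²·N·m/(1−ρ) = 0.0625 × 66 × 2/0.5 = 16.5
- df1 = (k−1)(m−1) = 2 and df2 = (N−k)(m−1) = 63
- the noncentral F distribution gives power 0.953; N = 63 gives 0.944

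So 66 is the smallest balanced N that reaches 0.95, and the article's figure is confirmed.

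**2. Rule out the other scale.** If f = 0.25 were the f behind SPSS's η²p, then λ = f²(N−k), or f²N in a common variant, without the factor 4. The smallest balanced N for 95% power would be 255 or 252. Only the default scale gives 66. The 0.80 in "The statistical power is set at 0.80" does not explain 66 either: for 80% power the default scale needs 42 and the SPSS scale 159–162.

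**3. Convert the planned effect.** η²p = λ/(λ+N) = 16.5/82.5 = 0.20 (0.208 with the error df of 63 in place of N). Then f = √(0.20/0.80) = 0.50. By contrast, f = 0.25 on this scale is η²p = 0.0625/1.0625 = 0.059.

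**4. Check through change scores.** With two time points the interaction is a one-way comparison of changes.
- SD of change = σ√(2(1−ρ)) = σ at ρ = 0.5.
- A cell-mean f of 0.25 puts the SD of the three mean changes at 2 × 0.25σ = 0.5σ.
- Hence f = 0.50 and λ = 66 × 0.25 = 16.5, as before.
- One group apart from two equal groups: difference = 0.5 × 3/√2 = 1.06 SD. Three equally spaced groups: range = 2 × 0.5 × √1.5 = 1.22 SD.

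**5. Power at the SPSS-scale f of 0.25 (η²p = 0.059).**

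| Analysed | λ = f²(N−k) | λ = f²N |
|---|---|---|
| 66 | 0.393 | 0.409 |
| 76 | 0.450 | 0.466 |

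Simulating change scores with 22 per group (20,000 runs) gave 0.951 for the planned effect and 0.411 for f = 0.25 on the change-score scale.

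**6. Effect detectable with 80% power at N = 66.** The required λ is 10.1. This gives η²p = 10.1/76.1 = 0.133, f = √(10.1/66) = 0.39, and a one-group difference of 0.39 × 3/√2 = 0.83 SD.

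**7. Dependence on ρ**, holding cell-mean f = 0.25 and N = 66:

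| ρ | implied η²p | power |
|---|---|---|
| 0 | 0.11 | 0.71 |
| 0.3 | 0.15 | 0.86 |
| 0.5 | 0.20 | 0.953 |
| 0.7 | 0.29 | 0.998 |

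The correlation changes which η²p a cell-mean f of 0.25 stands for. The η²p that 66 participants can detect with 95% power stays at about 0.20, because that depends only on λ and the degrees of freedom.

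**The case against.** The best defence is that nothing has been miscalculated. The stated inputs reproduce 66 exactly, and f = 0.25 can be called medium on the cell-mean scale to which G*Power applies it. The Statistical analysis section names partial eta squared as a reporting measure but sets no target on it and calls no value of it medium. All of this stands. A reader might infer an arithmetic error or a mis-sized trial, and the documents support neither. Calling 0.20 a large effect would also rest on a cut-off that the article does not print.

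It can also be said that the harm is limited. The article does not say that a null result excludes a medium effect, and it plans Bayes factors, which bear on non-significant results. Nor would an observed partial eta squared of 0.06 pass for a positive finding: with 2 and 63 degrees of freedom it gives F = 2.01 and p = 0.14, and significance needs at least 0.091. These points lower the stakes. They do not supply the missing scale, and Bayes factors do not tell the reader which effect the design was powered for.

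Finally, 0.20 depends on the assumed correlation, and no SD for the skill scores is given, so no figure in shots can be defended. Both are accepted. Even at ρ = 0 the implied value is 0.11, well above 0.059.

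**Conclusion.** The concern holds as a misstated power property, not as an arithmetic fault. At the protocol's own correlation of 0.5, the effect behind the 95% claim is an interaction partial eta squared of about 0.20. In SD units it is one group about 1.06 SD from the other two in mean change. Because randomisation makes the groups equal at baseline in expectation, that is also the expected size of the post-test difference in outcome SDs, which is the kind of quantity the planned Cohen's d describes.

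For an f of 0.25 on the reporting scale, the trial has roughly 40% power with 66 analysed and at most about 47% with 76. The unqualified statement of 95% power for a medium effect is therefore not true on the scales on which results will be given.

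This rests on G*Power's default option having been used. The article does not name it, but it is the option that reproduces 66. It also rests on equal variances and on ρ = 0.5. The point does not show that 66 is too few: that depends on which effect is worth detecting, and the article gives no basis for judging it.

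**What to change.** Keep the sample size and restate the Participants paragraph along these lines: f = 0.25 is on the G*Power default (cell-mean) scale; with a correlation of 0.5, N = 66 gives 95% power for an interaction partial eta squared of about 0.20 (one group differing from the other two by about 1.06 SD in mean change) and 80% power for about 0.13 (about 0.83 SD).

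Remove the unqualified word medium, or tie it expressly to the cell-mean scale. Add that a non-significant interaction will not be read as excluding a medium effect on the partial eta squared scale. Give no equivalent in shots unless an SD for the skill tests can be sourced.

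The cost is one rewritten paragraph and a less favourable power statement. No participants, outcomes or tests change, and the article states that recruitment had not begun.

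### The recruitment target of 76 falls one or two golfers short of the stated minimum of 66 after 15% dropout, and the planned power is given as both 0.95 and 0.80

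*Protocol article*

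**What the plan says.** In the protocol article, Participants, the sizing target is the interaction: "the sample size calculation is based on the statistical power required to detect a time × group interaction effect". The inputs follow: "Assuming a medium effect size f = 0.25 (Cohen’s standard), α = 0.05, power = 0.95", with "three groups, two measurement time points, and an intra-class correlation (ICC) of 0.5". The result is that "the study requires at least 66 participants (22 per group) to ensure sufficient power". The allowance for losses comes next: "Considering a potential dropout rate of 15% [51], a total of 76 golfers will be recruited".

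The Statistical analysis section names the same time × group interaction as the core hypothesis, but gives a different power: "The statistical power is set at 0.80, and all analyses will be performed using IBM SPSS Statistics 27.0". It does not say that 0.80 is a floor, or that it belongs to another test or outcome.

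**The concern.** Two stated figures do not agree with the rest of the sample-size argument.

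- **Dropout.** The recruitment target exists to leave at least 66 evaluable golfers after 15% are lost. The step from 66 to 76 looks like an addition of 15% to the evaluable number. Dropout, however, removes 15% of the recruited number. If so, the target misses the minimum it was built to protect.
- **Power.** One trial and one core hypothesis carry two power values. Power of 0.95 and power of 0.80 imply quite different sample sizes, so one statement must be wrong or refer to something unexplained. The value also matters for judging a shortfall, because the Participants section allows for recruitment ending slightly below plan.

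**Working it through.** **Inputs** (all from Participants, except the second power value, which is from Statistical analysis): f = 0.25; α = 0.05; k = 3 groups; m = 2 time points; correlation ρ = 0.5; power 0.95 (or 0.80); required N = 66; dropout d = 0.15; recruited 76.

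**Formula for the within–between interaction, noncentral F:**

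- λ = f² × N × m / (1 − ρ)
- df1 = (k − 1)(m − 1) = 2
- df2 = (N − k)(m − 1) = N − 3

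**Step 1: reproduce the 66.** λ = 0.0625 × 66 × 2 / 0.5 = 16.5, with df 2 and 63. Power is 0.9535. At N = 63 power is 0.9436, so 66 is the smallest multiple of three that reaches 0.95. The plan's figure is confirmed.

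**Step 2: size at 0.80.** On the same inputs, N = 42 gives λ = 0.0625 × 42 × 2 / 0.5 = 10.5, with df 2 and 39, and power 0.803. This is the smallest N that reaches 0.80. The two power statements therefore correspond to 66 and 42 evaluable golfers, a difference of 24. The 66 belongs to 0.95.

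**Step 3: reproduce the 76.** 66 × 1.15 = 75.9, rounded up to 76. Dividing by the retained fraction gives 66 / (1 − 0.15) = 77.65, so 78.

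**Step 4: what each target leaves.**

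| Recruited | Expected completers at 15% loss | Against 66 |
|---|---|---|
| 76 | 76 × 0.85 = 64.6 | 1.4 short |
| 78 | 78 × 0.85 = 66.3 | met |

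The largest loss that 76 can absorb is (76 − 66)/76 = 10/76 = 13.2%.

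**Step 5: power with the likely completers.** The equal-group formula, used here as an approximation for numbers not divisible by three, gives:

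| Completers | Power |
|---|---|
| 64 | 0.9471 |
| 65 | 0.9504 |
| 66 | 0.9535 |

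**The case against.** The strongest reply is that nothing of substance turns on either error, and most of that stands.

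- **Power is almost untouched.** At 65 completers the planned 0.95 is still reached, and at 64 it is missed by about 0.003. The minimum of 66 partly reflects rounding to equal groups, since the formula already passes at 65.
- **The plan softens a small shortfall.** It expects the closed camp to limit dropout. It would fit mixed-effects models by maximum likelihood when data are missing, so a golfer with only a baseline test need not be wholly lost. It also says how a slightly smaller sample would be reported. That last provision concerns resource constraints rather than dropout, so it answers only in part.
- **The sizing basis can be recovered.** Only 0.95 is tied to a calculation, and recruitment follows the larger number.

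None of this makes the two figures correct: 76 does not cover the stated 15% on the stated minimum, and 0.80 conflicts with 0.95.

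A reader might also object that 76 cannot be divided equally by three. The document does not support that as an error. It gives 22 per group for the 66 evaluable golfers only and promises no equal split of the 76. A 26/25/25 allocation would cost almost no power, and the allocation detail may be left to the full protocol.

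**Conclusion.** The point holds as a minor correction of stated figures. The recruitment target is two below what the plan's own dropout assumption requires (76 against 78), leaving 64 or 65 completers against a minimum of 66, with power of about 0.947 to 0.950. The power of 0.80 in Statistical analysis contradicts the 0.95 in Participants. The 66 itself is right.

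A reader might infer that the trial is underpowered, or that its size is uncertain by 24 golfers. Neither follows. The loss of power is at most about 0.003 below target, and the evaluable number was plainly computed at 0.95.

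These results take the plan's f, α and correlation as given, read the 15% as a share of those recruited, and treat golfers who drop out as contributing nothing to the interaction test.

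**What to change.** 1. **Dropout.** Keep 76 and restate what it covers: about 13% dropout with 66 completers, or power of about 0.947 to 0.950 if 15% are lost. Alternatively, if two more golfers are readily available, state 78.
2. **Power.** In Statistical analysis, replace 0.80 with 0.95, or say which test or threshold the 0.80 refers to.

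The cost is two edited sentences, plus two further participants only if 78 is chosen. The design and the analysis do not change. The article reports that neither recruitment nor data collection had begun when it was written.
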